### Intervention period data

During the study intervention, parameters are recorded daily at the same hour (the time of assessment is set by the local trial coordinator) within two hours of tolerance: SOFA score, ventilator mode, minute ventilation, respiratory rate, tidal volume, peak airway pressure, mean airway pressure, level of pressure support, set level of variability of pressure support, PEEP, airway inspiratory occlusion pressure at 100 ms (P0.1), FiO_2_, PaO_2_, PaCO_2_, pH, number of changes of pressure support settings, PEEP settings and FiO_2_ settings per 24 h, heart rate, mean arterial pressure, temperature, medication received in the last 24 hours (including sedatives, analgesics, neuromuscular blocking agents, corticosteroids and catecholamines) and fluid balance for the last 24 hours (including crystalloids, colloids and blood products). Selected centers will record the variation of tidal volume, pressure support, respiratory rate, inspiratory and expiratory times, as this requires additional equipment not available to all centers.

Because of logistical and organizational factors not every patient can be extubated immediately upon fulfilment of the extubation criteria (for example, at night). Therefore, the date and time of fulfillment of the extubation criteria and when extubation was performed are recorded separately. Successful extubation is documented after 72 hours of monitoring as explained before. With every extubation the intensive care delirium screening checklist score is assessed.

The need for NIV, NIV CPAP level and NIV pressure support level, as well as the total number of NIV hours, will be recorded. Incidences of tracheostomy and self-extubation will be registered.

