### Extubation criteria

As the ventilator settings are reduced in a stepwise manner to reach the extubation criteria, the patient’s condition is continuously monitored. As soon as the patient fulfills the following extubation criteria for a time period of at least 30 minutes, extubation is possible:

Richmond agitation and sedation scale (RASS) ≥ −3; behavioral pain scale (BPS) ≤5 or visual analogue scale (VAS) for pain ≤3; raising hands or legs against gravity; temperature ≥36°C and ≤39°C; ability to cough to clear secretions after deflating cuff; respiratory rate 8 to 30/min; PaO_2_/FiO_2_ ≥ 200 mmHg (≥150 mmHg in patients with chronic obstructive pulmonary disease); pressure support ≤8 cmH_2_O; PEEP ≤8 cmH_2_O; systolic blood pressure 80 to 160 mmHg; heart rate 40 to 130/min and no hemodynamically relevant arrhythmia.

If extubation has occurred and the patient needs to be re-intubated within 72 hours, the extubation is defined as not successful and the assigned study mechanical ventilation mode will be reinstituted as soon as possible. Successful extubation is defined as extubation lasting 72 hours.

Non-invasive ventilation (NIV) after extubation is allowed after extubation according to local practice. However, if a PEEP level >8 cmH_2_O, or pressure support >8 cmH_2_O is required for NIV, the extubation is considered not successful.

If the patient has to receive tracheotomy during the study period, assisted mechanical ventilation will be resumed as soon as possible via the tracheal cannula according to the assigned therapy group. In tracheotomized patients successful extubation is defined as patient separation from the ventilator without reconnection for <72 h after separation. If continuous positive airway pressure (CPAP) therapy via the tracheal cannula with PEEP >8 cmH_2_O or pressure support >8 cmH_2_O is required, the separation from the mechanical ventilator is considered not successful. The study-related intervention is finished on successful extubation. Patients will be observed until ICU and hospital discharge and contacted during the follow-up period.

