### Study endpoints

The primary endpoint is weaning time, defined as the time from randomization to successful extubation.

Secondary endpoints are: total time of mechanical ventilation; time from randomization to first extubation; time from randomization to fulfillment of extubation criteria; time between fulfillment of extubation criteria and extubation; ICU length of stay, in-hospital length of stay; ICU and in-hospital-mortality; mortality at day 90 and 6 months; PaO_2_/FiO_2_; PaCO_2_; total minutes of ventilation; mean tidal volume; mean pressure support; mean airway pressure; mean peak inspiratory pressure; inspiratory airway occlusion pressure at 100 ms; visual analogue scale for breathing comfort; cumulative amount of sedative and analgesic drugs; SOFA score; re-intubation rate; use of non-invasive ventilation; post-extubation duration of NIV; ventilator-free days (28 days); number of changes in mean pressure support by ICU personnel; coefficients of variation of tidal volume and pressure support; respiratory rate, and inspiratory and expiratory times.

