The ViPS trial will broaden our knowledge of the impact of variable PSV on important clinical outcome variables in a mixed ICU population. The inclusion and exclusion criteria have been carefully designed to include a large number of patients, regardless of their co-morbidities, while taking safety issues into account. Thereby, the use of variable PSV, which has been evaluated only for hypoxemic lung failure, will be expanded to other patient groups. The protocol described here represents a consensus among centers and investigators with considerable experience in weaning patients from mechanical ventilation. The interventions are an agreement between several weaning strategies conducted in the participating centers, while the variable PSV settings have been carefully derived from experimental knowledge combined with clinical experience. Therefore, compliance of the participating centers to the protocol is likely.

The ViPS trial protocol has limitations that must be addressed. First, the entry criteria allow for patients with large differences in weaning duration, ranging from hours to days. These differences have been considered in the sample size calculation. Second, patients who fail to wean may be transferred to weaning centers, resulting in them being lost to follow-up and, consequently, causing a reduction in study power. Nevertheless, the dropout rates considered in the sample size calculation represent a worst case scenario for the participating centers. Third, the protocol cannot be conducted in a blinded fashion, which can favor bias. To minimize this effect, we defined a tight protocol where intervention steps mandate handling until the primary endpoint is achieved. Fourth, even though the protocol interventions represent a consensus among centers, local differences in weaning experience and standards may still affect the results of this trial. Fifth, the use of non-invasive ventilation following extubation could introduce bias in terms of a reduction of weaning time, but this effect should not affect the comparative performance of variable PSV, since it is also allowed in the control group.

In conclusion, ViPS is the first randomized controlled trial that compares variable with non-variable PSV with respect to the duration of weaning from mechanical ventilation in a mixed ICU population. This trial may also clarify how and why variable PSV improves lung functional variables, and reduces the respiratory drive.

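### On-treatment records follow a fixed daily hour, not randomization or extubation, so the first drug window can predate randomization and fast weaners can have no record

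*Protocol article*

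**What the plan says.** Under Intervention period data, the Protocol article sets one on-treatment record a day: "parameters are recorded daily at the same hour (the time of assessment is set by the local trial coordinator) within two hours of tolerance". The period covered is the intervention itself ("During the study intervention, parameters are recorded daily"), and under Extubation criteria "The study-related intervention is finished on successful extubation".

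Two kinds of window are used. Drugs are entered as "medication received in the last 24 hours", and fluid balance has the same look-back. Setting changes are entered as "number of changes of pressure support settings, PEEP settings and FiO_2_ settings per 24 h", which is a rate and not a stated look-back.

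Under Study endpoints, the "cumulative amount of sedative and analgesic drugs" and the number of pressure-support changes are secondary endpoints, as are PaO2/FiO2, PaCO2, mean pressure support and P0.1. No time window is given for any of them. The Discussion accepts that "the entry criteria allow for patients with large differences in weaning duration, ranging from hours to days".

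Three records are tied to the patient's own course: ventilator and blood-gas values before and after the pre-inclusion test (Baseline data), the delirium score at each extubation, and the times at which extubation criteria were met and extubation took place.

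**The concern.** The endpoints are meant to describe what happened between randomization and extubation, but the recording grid is not cut at either event. Three things follow if the rule is applied as written.

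- The first drug and fluid window takes in hours before randomization, mostly under controlled ventilation and its sedation. The article sets no record for the hours between the last daily time and extubation.
- A patient randomized after one day's recording time and extubated before the next has no on-treatment value. An analysis plan cannot recover what was never collected. The last-observation-carried-forward rule (Statistical analysis) would have only the pre-inclusion-test values to carry, and that list contains neither pressure-support level nor P0.1.
- Later daily values exist only for patients still ventilated. If one arm weans faster, its remaining patients are a more heavily selected group.

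At stake are the drug-exposure comparison and the physiological comparisons that the Discussion hopes will show how variable PSV works.

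**Working it through.** **The plan's own figure.** The article gives no figure for recording. Its sample size reproduces: 2 × (1.960 + 0.842)² × (5/2)² = 98.1, so 99 per group; dividing 99 by the Wilcoxon efficiency 3/π gives 103.7, so 104; 2 × (104 + 10) = 228. Nothing below changes it.

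**Inputs from the article.** One record every 24 h at a set hour; a 24 h look-back for drugs and fluids; weaning from hours to days; SD 5 days in both groups and a hypothesised 2-day difference (Sample size calculation).

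**Assumptions.** U, the hours from randomization to the first daily record, is uniform on 0 to 24. No record is made at or after extubation. The two-hour tolerance is ignored. T is the hours from randomization to extubation.

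**Step 1, no record.** For T < 24, P(U > T) = 1 − T/24.

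**Step 2, pre-randomization hours counted.** The first window contains 24 − U such hours. For T ≥ 24 the mean is 24 − 12 = 12 h. For T < 24, a patient with a record has a mean of 24 − T/2. Counting patients without a record as zero, the mean is (T/24)(24 − T/2).

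**Step 3, final hours missed.** For T ≥ 24 the time from the last record to extubation is uniform on 0 to 24, mean 12 h. For T < 24 the mean equals that in Step 2. At T = 6, for example, 0.75 × 6 + 0.25 × 3 = 5.25 h.

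| T | No record | Mean pre-randomization hours counted (= mean final hours missed) | As share of T |
|---|---|---|---|
| 6 h | 75% | 5.25 | 88% |
| 12 h | 50% | 9 | 75% |
| 18 h | 25% | 11.25 | 63% |
| 24 h | 0 | 12 | 50% |
| 48 h | 0 | 12 | 25% |
| 72 h | 0 | 12 | 17% |
| 120 h | 0 | 12 | 10% |

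The two errors balance, so average recorded time equals average weaning time. Earlier hours replace the last hours; there is no net gain or loss of hours.

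**Step 4, trial-wide share with no record.** The article gives no mean weaning time, so means are assumed, with SD 5 days (simulation):

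| Assumed mean | Gamma | Lognormal |
|---|---|---|
| 3 days | 38% | 16% |
| 5 days | 9% | 2% |
| 7 days | 1% | 0.1% |

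Reading adjacent rows as two arms 2 days apart shows how unequal the loss could be. Means of 5 and 3 days give 9% against 38% (gamma) or 2% against 16% (lognormal). Means of 7 and 5 days give 1% against 9%, or 0.1% against 2%.

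**Step 5, setting changes.** Pressure support before randomization is limited to the one-hour pre-inclusion test and any repeats, so few changes could be counted from that time. The fault is the denominator: changes made during the first U hours are set against 24 h, which scales the rate by U/24 (a quarter of its true value at U = 6). The partial last day has the same problem.

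**The case against.** The strongest reply is that one sentence in a condensed article is being pressed hard, and that some inferences a reader might draw are not supported. Much of this stands.

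- **Setting-change counts include pre-randomization time.** Not supported: the look-back wording applies to drugs and fluids only, and Step 5 shows how little could be counted.
- **The final hours are certainly lost.** Not established. The intervention ends at successful extubation, defined as lasting 72 hours, so daily records might continue after the tube is out. A further look-back would then cover the last hours, but would add post-extubation hours. The window would still not match the weaning period.
- **Each site has one clock time.** The coordinator could set the hour per patient, even at the hour of randomization. Nothing requires it, but the uniform delay remains an assumption.
- **The error in drug totals is larger in the faster arm.** Not in hours: the mean is 12 h for any wean of 24 h or more, and less for shorter ones. Only the share grows. Pre-randomization exposure is also balanced in expectation by randomization.
- **Nothing is anchored to the patient.** The pre-inclusion-test record comes shortly before randomization, but it is not on treatment.
- **Any on-ventilator measure is limited to patients still ventilated.** True, and how daily values are summarised belongs to the analysis plan. An early value that was never collected cannot be supplied there.

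The full protocol or case report form may also define the first and last windows. The article nevertheless states a recording rule outright, and that rule leaves both ends open.

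**Conclusion.** The point holds in limited form. As written, the first drug and fluid window includes pre-randomization hours, the article sets no closing record before extubation, and patients weaned within hours may have no on-treatment value for named endpoints.

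Under a uniform 0 to 24 h delay, the size is 12 h of misplaced time on average for weans of 24 h or more, and a probability of 1 − T/24 of no record below that. The trial-wide share without a record cannot be fixed from the article; 0.1% to 38% is the range over the assumed means and distributions.

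If variable PSV brings more patients under 24 h, the loss is commoner in that arm, and PaO2/FiO2, PaCO2, P0.1 and mean pressure support are compared among differently selected patients. If it shortened only long weans that stayed above 24 h, the no-record share would not differ, but selection on later days would remain.

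A reader might infer that the main result is threatened. It is not: extubation times are recorded separately, the sample size is unaffected, and the endpoints concerned are exploratory secondary ones.

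**What to change.** 1. Start the first drug, fluid and setting-change window at randomization, keep 24 h windows after that, and add a closing window from the last daily record to extubation. Report totals together with rates per ventilated day, using the actual length of each window as denominator.
2. Add one record of ventilator values, including pressure support and P0.1, at a fixed early time after randomization in every patient, with the routine blood gas nearest in time. Two hours is an example; the time should be early enough that almost nobody has been extubated. Use this record as the between-arm physiological comparison free of selection, and keep the daily values as descriptive.

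The cost is case report form wording and a few minutes of extra data entry per patient. Drug totals come from existing charts and no extra blood sample is needed. Treatment, the primary analysis and the sample size do not change.

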### Study dropouts

Participation in the trial is voluntary. A subject has the right to withdraw from the study at any time for any reason without any consequences for further medical treatment. Furthermore the investigator has the right to terminate the participation of any subject at any time, if the investigator deems it in the participant’s best interest. The reason and circumstances for study discontinuation will be documented in the participant’s case report form (CRF). Any subject who discontinues participation and has been treated according to the study protocol should undergo a final examination if possible. The result of the final examination will be documented in the CRF and the data analyzed according to the intention-to-treat principle.

### Follow-up

The duration of ICU and hospital stay as well as the discharge destination are recorded. Patients will be contacted by telephone to assess their quality of life during the follow-up period at 28 days, 90 days and 6 months.

### Study endpoints

The primary endpoint is weaning time, defined as the time from randomization to successful extubation.

Secondary endpoints are: total time of mechanical ventilation; time from randomization to first extubation; time from randomization to fulfillment of extubation criteria; time between fulfillment of extubation criteria and extubation; ICU length of stay, in-hospital length of stay; ICU and in-hospital-mortality; mortality at day 90 and 6 months; PaO_2_/FiO_2_; PaCO_2_; total minutes of ventilation; mean tidal volume; mean pressure support; mean airway pressure; mean peak inspiratory pressure; inspiratory airway occlusion pressure at 100 ms; visual analogue scale for breathing comfort; cumulative amount of sedative and analgesic drugs; SOFA score; re-intubation rate; use of non-invasive ventilation; post-extubation duration of NIV; ventilator-free days (28 days); number of changes in mean pressure support by ICU personnel; coefficients of variation of tidal volume and pressure support; respiratory rate, and inspiratory and expiratory times.

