## Background

Around 40% of the total duration of mechanical ventilation is spent in the weaning process [1-3]. Both prolonged mechanical ventilation, as well as premature extubation, are associated with severe complications. For example, the risk of developing pneumonia increases with the duration of mechanical ventilation [4,5] and with re-intubation [6]. More importantly, failed extubation is associated with an increase in the risk of death [7]. Therefore, delivery of mechanical ventilatory support for the shortest possible time is the state of the art in intensive care medicine [8].

Pressure support ventilation (PSV) is the commonest form of spontaneous assisted mechanical ventilation worldwide [3]. During weaning with PSV, the pressure support applied by the ventilator is reduced in a stepwise manner until a minimal level of support is achieved. During classical (non-variable) pressure support, each spontaneous breath is supported by a constant set level of pressure at the airways. Thus, breath-by-breath variability of tidal volume (*V*_
*T*
_) and respiratory rate (RR) is mainly determined by the patient’s respiratory drive. A low respiratory drive, due to underlying disease and/or deep sedation, may result in a respiratory pattern with minimal or no variability despite the spontaneous breathing.

Decreased variability in *V*_
*T*
_ and RR is associated with delayed weaning from mechanical ventilation in a mixed intensive care unit (ICU) population [9]. In patients recovering from sepsis, increased variability of *V*_
*T*
_ and RR is a reliable predictor of weaning success [10]. However, those studies were conducted retrospectively and, to our knowledge, no study has tested whether weaning from mechanical ventilation can be made shorter by increasing the variability of the tidal volumes using variable levels of pressure support. A possible reason for the lack of such a study might be because assisted modes of mechanical ventilation resulting in more variable respiratory patterns (for example, proportional assist ventilation and neurally adjusted ventilatory assist) depend on the intrinsic variability of the respiratory system. Another likely explanation is that a desired mean *V*_
*T*
_ is difficult to guarantee in closed-loop systems that sense the inspiratory effort, making comparisons of variable with non-variable assisted mechanical ventilation at a predefined mean *V*_
*T*
_ difficult.

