### Baseline data

After screening the following demographic characteristics will be documented: patient’s age, sex, height, weight, predicted body weight, date and type of hospital admission, date and type of surgery, date of ICU admission and time of mechanical ventilation. If a patient meets the inclusion and exclusion criteria we record the following: acute physiology and chronic health evaluation (APACHE) II score and sequential organ failure assessment (SOFA) score. Before and after the pre-inclusion test we record the following: date and time of pre-inclusion test, ventilation mode before and after pre-inclusion test, minute ventilation, respiratory rate, tidal volume, peak airway pressure, mean airway pressure, PEEP, FiO_2_, PaO_2_, arterial partial pressure of carbon dioxide (PaCO_2_) and pH.

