### Statistical considerations

#### Sample size calculation

The sample size calculation (GPower software version 3.1.3, University of Düsseldorf, Germany) was based on the Wilcoxon–Mann–Whitney test (two groups, two tailed). The calculation was based on the expectation that the primary endpoint variable (time from randomization to successful extubation) would show a difference of 2 days between the two treatment groups. Based on the study by Lellouche *et al*. [14] the standard deviation (SD) was estimated as 5 days for both groups, yielding an effect size (*d*) of 0.4. Accordingly, 104 patients per group would allow the detection of differences between the groups with a power of 80% and a type one error rate of 5%. Assuming that 10 dropouts per group may occur, 228 patients in total are necessary.

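### Total ventilation time, read naturally, includes time before randomization that treatment cannot change; an unadjusted comparison will usually lose precision, without bias

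*Protocol article*

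**What the plan says.** The article's Study endpoints section starts the primary endpoint at randomization and does the same for two secondary endpoints, first extubation and fulfilment of the extubation criteria. The first secondary endpoint differs. The list reads "total time of mechanical ventilation; time from randomization to first extubation", and only the second item has a start point. The same list gives "ICU length of stay, in-hospital length of stay", also without a start. The Follow-up section adds only that "The duration of ICU and hospital stay as well as the discharge destination are recorded".

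Three other places bear on how to read the word total:

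- **Background:** "Around 40% of the total duration of mechanical ventilation is spent in the weaning process". Here the total means the whole course of ventilation, of which weaning is one part.
- **Inclusion and exclusion criteria:** every patient has had at least 24 hours of controlled ventilation, and no maximum is set. Randomization follows only after the pre-inclusion test, which can be failed and repeated.
- **Baseline data:** the recorded items include "date of ICU admission and time of mechanical ventilation", as well as the date of hospital admission.

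The Statistical analysis section calls the analysis of secondary endpoints exploratory. Continuous ones are compared by Student's t-test or the Mann–Whitney test, depending on a check of normality. The only multivariable model mentioned is a Cox regression attached to the overall survival curves.

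**The concern.** If the clock for total ventilation time starts when ventilation starts, each patient's value is the sum of two parts: time before randomization, fixed before allocation, and time after it, which is what variable pressure support is meant to shorten. An unadjusted two-group test carries the variance of both parts.

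For example, a patient ventilated 12 days before randomization and weaned in 2 scores 12 + 2 = 14. A patient ventilated 2 days before and weaned in 8 scores 2 + 8 = 10. The faster weaner gets the worse rank. Across randomized arms such reversals are noise, not a systematic distortion, but noise costs power.

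Readers will use ventilation duration and length of stay to judge whether faster weaning brings a wider benefit. A diluted comparison could show no clear difference although the hypothesized two-day effect is real, and could then be misread as contradicting the primary result.

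**Working it through.** **Inputs from the Sample size calculation section.** The primary endpoint "would show a difference of 2 days between the two treatment groups", with SD 5 days in each group (d = 2/5 = 0.40). The calculation uses a two-sided Wilcoxon–Mann–Whitney test and 104 patients per group, "with a power of 80% and a type one error rate of 5" percent.

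**Inputs not in the documents, so assumed.** The SD of ventilation time before randomization, s = 0 to 10 days, and its correlation with weaning time, r = −0.3, 0 or 0.5. The value s = 7.5 is 1.5 × 5: the 60:40 split implied by the Background figure, if both periods had the same coefficient of variation. Total time is taken as prior time plus weaning time.

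**Step 1: reproduce the plan.** Power comes from the noncentral t distribution with n multiplied by the relative efficiency of the Wilcoxon test under normality, 3/π = 0.955. The effective n is 104 × 0.955 = 99.3 per group, and the noncentrality is 0.40 × √(99.3/2) = 2.82. Power is 80.1%, and 104 is the smallest n that reaches 80%. With dropouts, 2 × (104 + 10) = 228, as stated.

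**Step 2: add the prior period.** Allocation cannot change it and randomization balances it in expectation, so the expected difference stays at 2 days. The SD becomes

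SD_total = √(5² + s² + 2·r·5·s), and d = 2/SD_total.

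For s = 5 and r = 0: √(25 + 25) = 7.07, d = 0.283, noncentrality 0.283 × √(99.3/2) = 1.99, power 50.9%.

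**Step 3: the range at 104 per group.**

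| Assumed s (days) | r = −0.3: SD, d, power | r = 0: SD, d, power | r = 0.5: SD, d, power |
|---|---|---|---|
| 0 | 5.00, 0.40, 80.1% | 5.00, 0.40, 80.1% | 5.00, 0.40, 80.1% |
| 2.5 | 4.87, 0.41, 82.1% | 5.59, 0.36, 70.8% | 6.61, 0.30, 56.4% |
| 5 | 5.92, 0.34, 65.9% | 7.07, 0.28, 50.9% | 8.66, 0.23, 36.7% |
| 7.5 | 7.66, 0.26, 44.8% | 9.01, 0.22, 34.3% | 10.90, 0.18, 25.1% |

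At r = 0, s = 1 gives 78.5% and s = 10 gives 24.1%. At r = 0, restoring 80% power would need 207 per group for s = 5 and 335 for s = 7.5.

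**Step 4: when nothing is lost.** The total is no more variable than weaning time when s² + 10·r·s ≤ 0, that is r ≤ −s/10. For s = 2.5, 5 and 7.5 this means r at or below −0.25, −0.50 and −0.75. With s = 0, a constant offset, neither the difference nor the ranks change, however long the prior period is.

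**Stay endpoints.** The documents give no effect size or SD for ICU or hospital stay, so no power is computed for them.

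**The case against.** The strongest objection is that the start point is inferred. The article never says when total ventilation time begins, and a full protocol or analysis plan may define it. That stands as a limit on certainty. The wording still favours the whole course: neighbouring items name randomization and this one does not, and the Background uses total in that sense.

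Second, the size of the loss depends on two quantities that the documents do not give. That also stands. With a small prior-time SD, or a modest SD and a mildly negative correlation, the loss is slight or absent. It is unlikely to be negligible throughout, because the prior period has no upper limit and the ICU population is deliberately mixed. Beyond a small SD, a gain needs a clearly negative correlation, with longer-ventilated patients weaning faster.

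A reader might infer something stronger: that about 60% of total time precedes weaning, so the endpoint hides a two-day effect. The documents do not support this. The 60% is a share of the mean and does not measure lost power, which depends on the variance and correlation. The 40% behind it is a general background figure, and the weaning process it describes need not begin at this trial's randomization. Nor is the comparison biased.

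Third, the consequences are limited. The secondary analyses are exploratory, the trial is sized for the primary endpoint only, and two other secondary endpoints already run from randomization. Ventilator-free days and re-intubation rate are also listed. This stands, although the two randomization-based times do not capture the full ventilation burden after randomization, including ventilation after a failed extubation. Total duration is also clinically meaningful in itself, which is a reason to keep reporting it.

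**Conclusion.** The point holds as one about precision. The planned comparison of total ventilation time most naturally includes a period that treatment cannot change, with no adjustment for it. Against 80% when counted from randomization, power for the same 2-day effect runs from about 82% down to 25% over prior-time SDs of 2.5 to 7.5 days and correlations of −0.3 to 0.5. At zero correlation it is 71%, 51% or 34%.

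These figures rest on the plan's 2 days and SD of 5 days, on 104 analysed per group, on a normal-theory approximation to the rank test, and on assumed values for the two missing quantities. For ICU and hospital stay the point applies only if they are counted from admission, and its size is unknown. The primary endpoint and the sample size are unaffected. This is a cheap improvement to exploratory endpoints, not an error that threatens the trial's main conclusion.

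**What to change.** State the start point of each duration endpoint. For the comparison between arms, do one of the following:

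- count ventilation time from randomization, including any re-ventilation; or
- keep the total as the tested quantity and adjust it for ventilation time before randomization, in a regression model that suits the distribution.

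Report the conventional total descriptively by arm in either case. If ICU and hospital stay are to be counted from admission, treat them the same way: test the time from randomization, or adjust for the stay before it, and describe the full stay.

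The cost is a change of wording. The ventilation time item and the admission dates are already listed as baseline data, and the time of randomization is needed for the primary endpoint. The small downside is that, under the first option, the tested figure is no longer the conventional total that other studies may report, which is why the total should still be shown.
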